### 2.6. Research Samples of Plasma and Sera

Plasma and sera samples are obtained from patients before AVF surgical creation and stored for further determination in the validated biobank MARENVU, at the laboratory of experimental nephrology, Faculty of Medicine, ULB.

For plasma preparation, we used 5 mL commercially available 3.2% citrate-treated tubes (light blue tops) from Becton Dickinson (BD) Vacutainer^®^ (Franklin Lakes, NJ, USA) Cells were removed from plasma by centrifugation for 15 min at 2000× *g* in order to deplete platelets in the plasma sample. The resulting supernatant (plasma) was then immediately apportioned into 0.5 mL aliquots using a clean polypropylene tube using a Pasteur pipette.

For serum preparation, we used a red topped 5 mL available tubes from Becton Dickinson (BD) Vacutainer^®^ for collection of whole blood. We waited 30 min at room temperature, in order to allow the blood clot formation. Sera was separated from blood by centrifuging at 1000–2000× *g* for 10 min in a refrigerated centrifuge. The resulting supernatant (serum) was then immediately apportioned into 0.5 mL aliquots using a clean polypropylene tube using a Pasteur pipette. Regarding storage and manipulation, plasma and sera are not analyzed immediately. All aliquots are stored and transported at −80 °C. Specific care is taken in order to avoid freeze–thaw cycles. When defrosted, sera are maintained at 2–8 °C while being handled. Samples which are hemolyzed, icteric or lipemic are excluded.

### 2.7. Patient Outcomes

Prospective follow-up is performed with a follow up of one year after AVF creation. AVF primary and secondary outcomes are listed in Table 2.

### 2.8. Statistical Analyses

The total expected sample size is assumed to be a minimum of 100 patients based on an average recruitment rate of 2 patients/month. Analyses will describe AVF clinical outcomes for patients with and without persistent aPL positivity, potential predictors of patient outcome. Analyses will use all available data, regardless of final sample size.

Data will be expressed as mean ± standard deviation (SD) for variables with a normal distribution or as median ± interquartile range (P25; P75). Student’s t-test will be used to compare the means of the quantitative variables following a normal distribution by group. The Mann–Whitney Wilcoxon test will be used to study the variation between two groups of variables following an asymmetric distribution. The significance level of the tests was 0.05 with odds ratios and 95% confidence intervals. Multivariate models will be performed through logistic regression for variables showing statistically significant differences between groups.

We will employ Kaplan–Meier survival analysis to estimate the probability of AVF primary patency and functional primary patency over time.

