Although ESKD is rare in APS, the prevalence of persistent aPL positivity is higher in HD patients compared to the general population, and can reach more than 35% [8]. The reason for such a high prevalence of aPL positivity in HD is not well known. Several hypotheses have been proposed such as (a) molecular mimicry as a response to the exposure to microorganisms, endotoxins or HD membranes, or (b) a response to oxidation (i.e., cross-reactive immunoglobulins against epitopes of oxidized lipids) [8]. Nevertheless, aPL positivity has been inconsistently associated with AVF thrombosis [8,9,10,11]. Also, aPL positivity has been rarely associated with AVF stenosis [12] and intrastent restenosis [13]. Recently, our group published the first report of a significant association between aPL persistent positivity, and native AVF maturation failure as defined by US in a retrospective study including 116 HD patients [14]. The aPL positivity was a strong predictor of AVF maturation failure in multivariate analysis.

The aim of the present study is to confirm this association in a prospective cohort. The primary outcome of the study is to examine the possibly causative link between aPL persistent positivity and the occurrence of AVF maturation failure defined by the clinical approach combined with US.

Secondary outcomes will focus on clinical outcomes other than AVF maturation: functional primary patency and primary patency, time to AVF complications, AVF thrombosis or stenosis rates, bleeding complications rates and HD adequacy parameters.

In addition, in order to better understand the underlying pathophysiological mechanism of AVF maturation failure in aPL positive patients, we will perform blood analyses as well as an in vitro study using cultured immortalized human microvascular endothelial cells type 1 (HMEC-1).

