## 2. Materials and Methods

### 2.1. Design and Objectives

This is a monocentric observational prospective cohort study that aims to recruit a cohort of 100 newly created native AVF in CKD patients with a previous aPL profile determination before AVF creation and HD initiation.

The sample size calculation was based on the assumption that the expected maturation failure rate in the general population is 50%, and is 70% in the aPL positive group. With alpha = 0.05, 1-Beta = 90%, and a two-sided test, 96 patients are required to detect a significant difference. Thus, we plan to enroll and analyze 100 patients.

Surgical AVF creation is performed as per standard of care without procedural variations between the aPL+ and control groups, ensuring homogeneity in the approach. No perioperative treatments or clinical assessments are specified by the study protocol.

Institutional Review Board authorization was obtained from the Brugmann University Hospital Ethics Committee (Reference number: CE2022/113), in accordance with the Declaration of Helsinki. Written informed consent is obtained from patients before any inclusion procedure. This study was registered on ClinicalTrials.gov (ID number: NCT06112821), and the study was started on August 2023. The study protocol is illustrated in Figure 1.

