**Figure 2 life-15-00168-f002:**
[figure not shown]
Pathophysiological hypothesis of aPL-associated AVF maturation failure. The first line represents the pathways implicated in the pathophysiology of APS and the second line represents the presentation of AVF maturation failure (either in the presence of thrombosis, stenosis or because of insufficient venous remodeling). The dashed arrows represent pathophysiological hypotheses that have not been studied in the literature, while the solid arrows represent associations described in the literature. MCP-1: Monocyte Chemotactic Protein 1, MMP: matrix metalloproteases, mTOR: mammalian Target of Rapamycin, NO: nitric oxide, TIMP-1: tissue inhibitor of metallo-proteinase-1.

**Table 1 life-15-00168-t001:** Baseline characteristics collected at the time of AVF surgical creation.

Parameters	
Demographics	Age
	Gender
	BMI (kg/m^2^)
	Ethnicity
	Smoking status
Treatments	Anti-platelet therapy
	ACE/ARBs
	Statins
	Erythropoietin
	Anticoagulation therapy
	Beta-blockers
Medical history	Etiology of CKD, histologically proven
	Diabetes mellitus
	Hypertension
	Coronary heart disease
	Stroke or TIA
	Ischemic heart disease
	Peripheral vascular disease
	Left ventricular ejection fraction
	Deep vein thrombosis (n, %)
	Other aPL related clinical features
Biological	Hemoglobin level
features	Platelet count, mean platelet volume
	Coagulation tests: activated PTT, fibrinogen, Prothrombine time
	Lipids
	c-reactive protein, ESR
	Nt-proBNP
Vascular access	Need for catheter before AVF use
parameters	AVF creation date, AVF type, surgical procedure information (type of anesthesia, artery and vein diameter, anastomosis diameter)
	Mapping details
	Perioperative complications: bleeding, local hematoma, other complications
	Pre-operative Flow mediated dilation of the brachial artery as a marker of endothelial dysfunction

ACE: angiotensin-converting enzyme inhibitors; ARB: angiotensin II receptor blockers; AVF: arteriovenous fistula; BMI: body mass index; CRP: c-reactive protein; TIA: transient ischemic attack.

**Table 2 life-15-00168-t002:** Primary and secondary outcomes.

Primary Outcomes	
AVF maturation	Defined 6 weeks after AVF creation, by US: AVF brachial artery blood flow > 600 mL/min, outflow vein diameter > 6 mm;

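### Choosing covariates by significance between groups can leave confounding in the adjusted aPL odds ratio, and may admit variables that should not be adjusted for

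*Protocol article*

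**What the plan says.** Section 2.8 (Statistical Analyses) gives one rule for the adjusted analysis: "Multivariate models will be performed through logistic regression for variables showing statistically significant differences between groups". The level comes from the sentence before it: "The significance level of the tests was 0.05 with odds ratios and 95% confidence intervals". The section names no covariate to be included whatever its p-value. It does not define the groups; the natural reading is aPL positive against aPL negative, because the same section says "Analyses will describe AVF clinical outcomes for patients with and without persistent aPL positivity, potential predictors of patient outcome".

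The Introduction sets the aim: "The primary outcome of the study is to examine the possibly causative link between aPL persistent positivity and the occurrence of AVF maturation failure".

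Table 1 lists the characteristics recorded at fistula creation. Many are ordinary candidate confounders, such as age, diabetes, peripheral vascular disease and vessel diameters. It also lists "Need for catheter before AVF use", perioperative complications, "Other aPL related clinical features", activated PTT, and pre-operative flow-mediated dilation as an indicator of endothelial dysfunction. The Discussion proposes endothelial dysfunction as the route from aPL to failed maturation.

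**The concern.** A confounder is defined by its relation to exposure and outcome, not by whether a test of imbalance reaches 0.05 in one sample. At this sample size such a test has little power, so a variable that biases the aPL comparison will often be left out. The result would still be presented as adjusted.

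The same rule has no filter for what a variable is. A screen on differences between aPL groups favours variables that lie close to aPL: its manifestations, assays that it alters, and steps on the causal path. Adjusting for these can remove part of the effect under study or inflate its standard error. At stake is the odds ratio on which the Discussion would base routine aPL screening before fistula creation.

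**Working it through.** **Inputs from the article.** The planned N is 100 (section 2.1) and the test level 0.05 (section 2.8). On outcome rates, section 2.1 assumes "the expected maturation failure rate in the general population is 50%, and is 70% in the aPL positive group"; the 50% is taken here as the rate in aPL-negative patients. The share of aPL-positive patients is not fixed for this cohort. The Introduction says prevalence in HD patients can exceed 35%, so 20%, 35% and 50% are used as an assumed range. Confounder prevalences and outcome odds ratios are also assumptions.

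**The plan's own figure.** The stated 96 patients does not reproduce. For 50% vs 70%, two-sided 0.05 and 90% power, the pooled two-proportion formula gives 124 per group, 248 in total. That is a separate matter and nothing below depends on it, except that a small N makes the screen weaker.

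**Step 1: chance that a real imbalance fails the screen.** For prevalences p0 and p1 in groups of n0 and n1, with p̄ the pooled prevalence:

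- SE0 = √[p̄(1−p̄)(1/n0 + 1/n1)]
- SE1 = √[p0(1−p0)/n0 + p1(1−p1)/n1]
- P(pass) = Φ[(|p1−p0| − 1.96·SE0)/SE1], and P(miss) = 1 − P(pass)

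Example, 40% vs 60% with n0 = 65 and n1 = 35: p̄ = 0.47, SE0 = 0.1046, SE1 = 0.1027. Then (0.20 − 0.2051)/0.1027 = −0.05, so P(pass) = 0.48 and P(miss) = 0.52.

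| Imbalance (aPL− vs aPL+) | Missed, 20% aPL+ | Missed, 35% aPL+ | Missed, 50% aPL+ |
|---|---|---|---|
| 30% vs 40% | 86% | 82% | 82% |
| 30% vs 45% | 74% | 68% | 66% |
| 40% vs 60% | 64% | 52% | 48% |
| 30% vs 50% | 60% | 49% | 47% |

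**Step 2: confounding left in the odds ratio.** 2,000 simulated studies per scenario, N = 100, 35% aPL positive, true aPL OR 1, three binary confounders each with outcome OR 2.5. Entries are the median aPL OR.

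| Imbalance per confounder | Unadjusted | Stated rule | Pre-specified set |
|---|---|---|---|
| 30% vs 45% | 1.46 | 1.21 | 1.01 |
| 30% vs 40% | 1.28 | 1.15 | 0.99 |

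At 20% and 50% aPL positive, the rule gives 1.16 to 1.22 and the pre-specified set 0.99 to 1.01. With a single 30% vs 40% confounder at 35% positive, the residue is small: 1.10 unadjusted, 1.05 under the rule, 1.00 pre-specified. Type I error under the rule stayed at about 4% to 7%.

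**Step 3: unsuitable candidates in Table 1.**

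- Catheter need before fistula use: section 2.2 enrols patients who have not started HD, so this can arise after fistula creation. Clinical maturation is defined in Table 2 by successful cannulation, so the two are closely linked.
- Perioperative complications arise at or after creation.
- Other aPL-related features are manifestations of the exposure. Section 2.3 uses clinical domains to define the APS subgroup.
- Activated PTT is a clotting time, and section 2.5 determines lupus anticoagulant by clotting assays.
- Flow-mediated dilation marks the article's own hypothesised mediator.

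**Step 4: power cost of admitting an aPL correlate.** Simulated at N = 100, 35% positive, aPL log OR 0.85, one 60%/40% confounder with log OR 1.0, and activated PTT shifted by an assumed amount in aPL-positive patients. Ranges cover repeated runs.

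| Assumed shift | Power, fixed model | Power, stated rule |
|---|---|---|
| 1.5 SD | 42–47% | 28–35% |
| 1.0 SD | 43–47% | 42–44% |
| 0.5 SD | 46% | 50% |
| 0 SD | 49% | 53% |

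**Step 5: room for covariates.** At 35% positive, expected failures are 35 × 0.70 + 65 × 0.50 = 57, leaving 43 non-failures. At ten per parameter that supports about four parameters. Over 20% to 50% positive the non-failures are 46 to 40.

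**The case against.** The sentence in section 2.8 does not contain the word only, leaves the groups undefined, and does not say that Table 1 is the candidate pool. Covariate detail is commonly left to an analysis plan that is not shown. The article also presents its analyses partly as descriptive and expects further studies to follow.

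Some of this stands. That Table 1 feeds the model is an inference, so the second half of the point is conditional. The first half is not: a selection rule is stated, and it is the rule that is at fault, not a missing detail. If the groups were matured against failed, confounders would still be screened by p-value and catheter need would be selected more readily.

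A reader might infer stronger claims that the article does not support:

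- **Catheter need is purely a result of failed maturation.** It can also reflect late referral or urgent dialysis before the 6-week assessment, and the article does not settle which.
- **aPL correlates must differ between arms.** The positive arm includes carriers without APS, and positivity can rest on aCL or aβ2-GPI alone, which need not prolong activated PTT.
- **The rule costs the study much of its power.** Step 4 shows a material loss only at a 1.5 SD shift, for which the article gives no data.
- **The rule inflates false positives.** Type I error stayed near nominal in step 2.

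**Conclusion.** The point holds in this form. The stated rule omits a real confounder with a 10 to 20 point imbalance in roughly 47% to 86% of studies of this size, so the adjusted aPL odds ratio can keep confounding. That range needs only N, the aPL split (assumed 20% to 50%) and the imbalance. The size of the remaining bias rests on assumed confounders: a median OR of about 1.2 instead of 1.0 with three confounders at 30% vs 45%, and less with one.

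If Table 1 is the candidate pool, the rule can also bring in post-creation variables, aPL manifestations or assay correlates, and a marker of the hypothesised mediator. This is a possibility, not a certainty. Its power cost is small unless the variable tracks aPL very strongly. Any bias from adjusting for the mediator or for catheter need was not put on a firm numerical footing, because the article gives no rates for it. The shown harm is a biased odds ratio that is labelled adjusted, which matters because the study reads it as evidence on causation.

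**What to change.** Replace the sentence in section 2.8 with wording such as:

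*The primary model is a logistic regression of maturation failure on aPL status with a small set of confounders fixed before analysis on clinical grounds. No covariate is selected by p-value. The primary model does not adjust for variables that arise at or after AVF creation, for manifestations or assay correlates of aPL, or for flow-mediated dilation.*

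The set should be small. Age, diabetes, AVF type and pre-operative vein diameter are one example. With the aPL term this makes at least five parameters, or about 43/5 = 8.6 non-failures each, slightly under the usual ten, so there is no room for a longer list. The exact set, and how antithrombotic medication is handled, are the sponsor's choice; that medication may relate to both aPL status and outcome and should be considered explicitly.

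The cost is wording only, since the candidate variables are already collected. The downside is that a short fixed set may leave out a variable that later proves imbalanced; it can be added in a sensitivity model.

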### 2.9. Future Analyses

To better understand the underlying pathophysiological mechanism of AVF maturation failure in aPL positive patients, we will perform blood analyses as well as an ex vivo study using cultured immortalized human microvascular endothelial cells type 1 (HMEC-1).

Blood samples:

The following markers of extracellular matrix (ECM) degradation will be assessed: matrix metalloproteases (MMP): MMP-2, MMP-9, tissue inhibitor of metallo-proteinase-1 (TIMP-1) and the ratio of MMP-2 and TIMP-1 will be evaluated and interpreted as a predictor of AVF maturation as prior described [15].

In Vitro study

HMEC-1 will be exposed to sera of aPL-positive patients and aPL-negative patients as controls. We will perform a comprehensive set of analyses across various biological process potentially implicated in the pathophysiology of AVF maturation failure. We will assess coagulation markers, inflammatory and leukocyte trafficking markers, complement system deposition and vascular tone, and metabolism-related markers and extracellular matrix degradation.

## 3. Discussion

AVF maturation failure is a frequent complication that occurs in more than half of cases after surgical creation of the AVF, and often requires the use of intervention [16], possibly leading to significant morbidity and mortality [1,2,16]. Therefore, a better understanding of the risk factors of AVF maturation failure is of importance in order to identify prophylactic or therapeutic strategies.

In the setting of persistent aPL positivity, AVF maturation failure could be related to early AVF thrombosis. Also, APS has been associated with endothelial dysfunction and intimal hyperplasia with stenotic lesions in some aPL-related manifestations such as APS nephropathy [17,18]. We recently described the association between aPL persistent positivity, and native AVF maturation failure defined by US. aPL positivity was a strong predictor in multivariate analysis; however, this association was independent of AVF stenosis or thrombosis during the maturation process [14]. These findings might suggest that aPL persistent positivity could be responsible for the inability of the efferent vein vasodilatation and remodeling leading to AVF maturation failure. However, these findings might also reflect the statistical artifact of combining two outcomes (i.e., AVF rachial artery blood flow and outflow vein diameter). Therefore, in order to confirm these results, we propose a prospective observational cohort study that aims to recruit a cohort of newly created native AVFs with a previous aPL determination and 12-week confirmation assays, with longitudinal clinical and US follow-ups. Analyses will describe AVF clinical outcomes, in terms of maturation, in patients with and without persistent aPL positivity, potential predictors of patient outcome. The results could have a significant clinical impact and pave the way for new exploratory or confirmatory studies.

Furthermore, we will further evaluate the pathophysiological mechanisms implicated in AVF maturation failure in the setting of aPL persistent positivity. After AVF creation, the efferent vein is exposed to oxygen-rich blood flow, but also to high shear stress, and high pressure. These changes will lead to morphological changes in both the arterial and venous wall (i.e., thickening and dilatation) [15]. Efferent vein remodeling is mediated by both venous endothelium and adventitia that sensor the hemodynamic forces change [19,20]. Initial phase implies the increase in MMP-2 and MMP-9, and the ratio of MMP-2 and TIMP-1 has been reported as a predictor of AVF maturation [15]. Also, other elastases such as cathepsin S and K are upregulated in the AVF, suggesting that elastin degradation is crucial in order to enhance efferent vein remodeling, by degrading the internal elastic lamina and basement membrane [21,22]. Also, numerous growth factors and cytokines play a crucial role in AVF maturation, particularly by regulating ECM synthesis or degradation, or by controlling cell proliferation and migration [15]. Interestingly, the expression of the MMP-2/-9 is decreased in the setting of aPL positivity, suggesting that MMPs can be involved in AVF maturation failure in the setting of aPL positivity [23].

Because aPL persistent positivity was associated with AVF maturation failure in the absence of stenosis or thrombosis, we hypothesize that endothelial dysfunction—through impaired NO release and/or decreased levels of MMPs or elastases—could be responsible for the inability of the efferent vein vasodilatation and remodeling leading to AVF maturation failure (Figure 2).

This study has the potential to significantly impact the clinical management of hemodialysis patients by identifying persistent antiphospholipid antibody (aPL) positivity as a predictive biomarker for arteriovenous fistula (AVF) maturation failure, along with a better understanding of the underlying pathophysiological mechanisms. If our findings confirm this association, routine screening for aPL positivity in patients planned for AVF creation could become a standard practice. This would allow early identification of high-risk individuals, enabling the implementation of preventive measures such as tailored anticoagulation strategies, closer clinical monitoring, or alternative vascular access planning.

This in vitro study has limitations. Cell-cultured conditions differ from physiological conditions, and isolated HMEC-1 cells do not reflect the complex AVF microenvironment composed of different cell types as well as their respective interactions. Cell cultures do not replicate blood flow and shear stress, which are crucial factors in AVF maturation, and cannot reproduce some pathological processes such as stenosis, intimal hyperplasia or thrombosis. Finally, HMEC-1 are microvascular immortalized cells and might limit the interpretation of molecular markers or results observed in an in vitro setting.

## 4. Conclusions

This observational prospective cohort study aims to prospectively examine the association between aPL persistent positivity and native AVF maturation failure in HD patients, potentially identifying antiphospholipid antibody (aPL) persistent positivity as a predictive biomarker for arteriovenous fistula (AVF) maturation failure. Patients’ plasma and serum samples will be collected before AVF creation and before HD initiation in order to further assess the underlying pathophysiological mechanisms. This study was registered on ClinicalTrials.gov (ID number: NCT06112821).

